## Abstract

**Background:**

Maintaining cerebral perfusion during anesthesia and intensive care is critical, yet the relationship between mean arterial pressure (MAP) and cerebral blood flow (CBF) remains poorly defined. In patients with aneurysmal subarachnoid hemorrhage (aSAH), pharmacologically induced hypertension is commonly applied to support cerebral perfusion, but its effects are uncertain.

**Methods:**

This protocol describes two parallel clinical studies using identical methodology. The first study population includes adults undergoing elective general anesthesia (MAP-ANE), and the second comprises sedated intensive care patients with aSAH (MAP-SAH). In both study populations, MAP will be increased stepwise with norepinephrine (NE) infusion under continuous invasive blood pressure monitoring, and CBF measured with phase-contrast MRI (PCMRI) and arterial spin labeling (ASL), while near-infrared spectroscopy (NIRS) will be performed in parallel to evaluate its validity as a surrogate marker. The primary outcome is the change in total CBF between baseline and elevated MAP, directly testing whether induced hypertension increases CBF. Secondary outcomes include ASL perfusion changes, the slope of the MAP–CBF relationship, systemic–cerebral hemodynamic correlations, and NIRS responses.

**Expected impact:**

These studies test the hypothesis that pharmacological MAP augmentation does not predictably increase CBF. By combining quantitative MRI with invasive monitoring, it aims to clarify MAP–CBF interactions, define the physiological basis of induced hypertension, and assess whether NIRS can serve as a clinically useful proxy. Findings are expected to inform safer and more individualized blood pressure management in perioperative and neurocritical care. The studies are registered at ClinicalTrials.gov (MAP-ANE: NCT06855407; MAP-SAH: NCT06033378).

**Trial registration:**

ClinicalTrials.gov, MAP-ANE NCT06855407, MAP-SAH NCT06033378

## Introduction

Tailoring blood pressure management to surgical procedure, clinical context, and comorbidities reduces the risk of organ dysfunction [1], but no consensus exists on intraoperative target levels, and the thresholds that define pathological blood pressure remain debated. A mean arterial pressure (MAP) of ≥65 mmHg is commonly assumed to be sufficient for organ perfusion [2], but individual patients may require higher levels depending on comorbidities.

In awake patients, the level of consciousness can serve as an indirect indicator of cerebral perfusion. Under general anesthesia or in critically ill patients, however, this assessment becomes considerably more challenging. This underscores the importance of understanding cerebral autoregulation, often illustrated by the classical model of Lassen (1959), which depicts a plateau of relatively constant cerebral blood flow (CBF) across a wide MAP range of approximately 60–160 mmHg [3]. More recent evidence demonstrates significant interindividual variability and a narrower plateau than originally described [4]. These uncertainties are clinically important not only in anesthesia, where hypotension frequently occurs, but also in neurological emergencies, which may present with both hypo- and hypertension [5] One such emergency is aneurysmal subarachnoid hemorrhage (aSAH), a life-threatening stroke caused by rupture of an intracranial aneurysm with bleeding into the subarachnoid space and, in some cases, extension into the brain parenchyma [6]. After treatment of the initial hemorrhage with endovascular coiling or surgical clipping, patients remain at risk of delayed cerebral ischemia (DCI) and associated neurological deficits during the early phase. [7]. In this setting, induced hypertension, an established therapy involving increase in blood pressure to supra-normal levels, is used to support cerebral perfusion [8,9]. Despite its frequent use, the evidence is limited, its effects on CBF remain uncertain, and the therapy carries risk [10].

Norepinephrine (NE) is the first-line vasopressor for restoring blood pressure in perioperative and critical care settings [11–13] and is also commonly used to achieve induced hypertension [14]. However, experimental and clinical studies, most relying on transcranial Doppler (TCD) flow velocity as a surrogate for CBF, indicate that NE-induced MAP elevation can have variable cerebrovascular effects depending on autoregulatory status. This reliance on surrogate markers leaves the net impact of NE on CBF unresolved [15,16].

Despite advances in understanding cerebral pathophysiology, clinical practice still relies primarily on MAP or, when intracranial pressure (ICP) is monitored, cerebral perfusion pressure (CPP) [17,18]. Bedside techniques such as near-infrared spectroscopy (NIRS) offer non-invasive, continuous monitoring of regional cerebral oxygenation (rSO_2_) [19]. However, because NIRS reflects surrogate markers of blood flow rather than direct measurements, it carries a risk of misinterpretation, particularly given that the relationship between MAP and CBF has not been fully characterized in different clinical contexts. Direct quantitative methods are therefore required. Advanced MRI techniques, notably phase-contrast MRI (PCMRI) and arterial spin labeling (ASL), provide non-invasive, contrast-free quantification of CBF. PCMRI enables measurement of blood flow rate (mL/min), vessel diameter, pulsatility, and flow direction in large cerebral vessels and is widely regarded as the gold standard for non-invasive quantification [20]. ASL provides regional cerebral perfusion measurements in mL/min/100 g and is widely used in clinical and research contexts [21]. Combined, PCMRI and ASL allow complementary quantification of CBF. When integrated with MAP and systemic circulation measures, this approach can yield valuable insights into the interaction between cerebral and systemic hemodynamics. We have recently demonstrated, using PCMRI, that induced hypertension with NE, raising MAP by approximately 20% in healthy individuals, paradoxically reduced CBF [22]. This finding challenges the assumption that MAP is a reliable surrogate for cerebral perfusion and provides strong motivation to extend investigation to patients under anesthesia and in critical illness.

This protocol describes two parallel studies applying identical MRI-based methodology in combination with continuous invasive blood pressure monitoring and NIRS: MAP-ANE in elective anesthesia patients and MAP-SAH in sedated ICU patients with aSAH. The objective is to characterize MAP–CBF relationships under these two conditions, test the hypothesis that blood pressure augmentation does not increase CBF, and explore interactions between the cerebral and systemic circulation. A further aim is to assess the validity of NIRS as a surrogate marker for CBF changes across different blood pressure levels.

## Materials and methods

### Study design

This study protocol follows the SPIRIT guidelines [23] and describes two non-randomized, prospective interventional studies with separate schedules for MAP-ANE and MAP-SAH (Fig 1 and 2). Graphical study flow diagrams (Fig 3 and 4) illustrate the process from screening and inclusion to completion of the intervention and, for ICU patients, return to intensive care. The design is within-subject and paired, with each participant serving as their own control by undergoing measurements at baseline MAP and after a standardized ~25% increase in MAP. No blinding is applied during the intervention. Participant recruitment for MAP-SAH began on October 6, 2023, and for MAP-ANE on December 6, 2024. Recruitment and data collection for MAP-ANE are expected to be completed by the end of 2026, whereas MAP-SAH is planned to continue until October 2030, with follow-up concluding at the same time. Data analysis and dissemination of results are planned during 2027 for MAP-ANE and following completion of MAP-SAH. No study results have yet been generated.

**Fig 1 pone.0338688.g001:**
[figure not shown]
SPIRIT schedule of enrollment, interventions and assessments for MAP-ANE (elective general anesthesia study population). MAP, mean arterial pressure; MMSE, Mini Mental State Examination; ABG, arterial blood gas; NIRS, near-infrared spectroscopy; PCMRI, phase-contrast magnetic resonance imaging; ASL, arterial spin labeling.

**Fig 2 pone.0338688.g002:**
[figure not shown]
SPIRIT schedule of enrollment, interventions and assessment for MAP-SAH (sedated ICU study population). MAP, mean arterial pressure; ABG, arterial blood gas; NIRS, near-infrared spectroscopy; PCMRI, phase-contrast magnetic resonance imaging; ASL, arterial spin labeling.

**Fig 3 pone.0338688.g003:**
[figure not shown]
Graphical study flow for MAP-ANE (elective general anesthesia study population). A. Screening and informed consent. B. Structural MRI and baseline PCMRI/ASL while awake without MAP increase. C. Ear, Nose and Throat surgery under general anesthesia followed by NIRS monitoring during a ~ 25% MAP increase with norepinephrine as a safety check to ensure tolerance without arrhythmias before MRI transport. D. Transport to MRI. E. PCMRI and ASL at baseline MAP and during a ~ 25% MAP increase with norepinephrine. F. Emergence from anesthesia and recovery.

**Fig 4 pone.0338688.g004:**
[figure not shown]
Graphical study flow for MAP-SAH (sedated ICU study population). A. Screening and inclusion with approval from both the ICU physician and the responsible neurosurgeon, and consent from next of kin. B. ICU care under sedation with NIRS monitoring during a ~ 25% MAP increase with norepinephrine as a safety check to ensure tolerance without arrhythmias before MRI transport. C. Transport to MRI. D. Structural MRI followed by PCMRI and ASL at baseline MAP and during a ~ 25% MAP increase with norepinephrine. E. Transport back to the ICU. F. Continued neurointensive care and monitoring.

### Study setting

The study is conducted at Umeå University Hospital, Umeå, Sweden. Documentation of all anesthetic and hemodynamic data is carried out in the hospital’s electronic patient data management system (PDMS) Metavision, version 6.8 (iMDsoft, Tel Aviv, Israel). Study-specific variables not captured in PDMS are recorded in paper-based case report forms (CRFs), which are securely stored in locked cabinets at the study site. MAP-ANE is conducted in the operating theatre setting during elective Ear, Nose and Throat surgery, and MAP-SAH is performed in the level 3 ICU (10 beds, with approximately 25% neurointensive care bed occupancy) among sedated patients with aSAH. The MRI examinations are carried out in the hospital’s 3T MRI unit, located on the same floor and equipped to enable examinations under general anesthesia.

### Recruitment and consent

Participants for the MAP-ANE and MAP-SAH studies are recruited at Umeå University Hospital, Umeå, Sweden, from patients undergoing elective general anesthesia and from sedated ICU patients with aSAH. The inclusion and exclusion criteria for both study populations are summarized in Table 1. Elective patients (MAP-ANE) will be enrolled preoperatively after providing written informed consent. For ICU patients (MAP-SAH), informed consent will be obtained from next of kin and subsequently confirmed by the patient if they regain decision-making capacity.

**Table 1 pone.0338688.t001:** Inclusion and exclusion criteria for the MAP-ANE (elective general anesthesia) and MAP-SAH (sedated ICU) study populations.

MAP-ANE	MAP-SAH
**Inclusion**	**Inclusion**
Age 50–80 years	Confirmed aSAH treated with endovascular coiling or surgical clipping
Elective Ear, Nose and Throat surgery under general anesthesia	Ongoing sedation with mechanical ventilation
Oral and written informed consent	Invasive arterial monitoring
Mini-Mental State Examination (MMSE) >23	Clinical stability sufficient to undergo MRI
ASA classification I–III	Informed consent obtained from next of kin
Completed cardiovascular and neurological screening	Exclusion
Structural MRI prior to intervention	MRI contraindications
**Exclusion**	Medical instability precluding transport to MRI
MRI contraindications (implanted devices, ferromagnetic metal/implants)	Tachycardia or bradycardia (heart rate >100 or <50 beats/min)
BMI > 30	High oxygen requirements (FiO2 > 60%)
	COPD stage 3–4
	BMI > 30
	Patient does not subsequently consent

aSAH, aneurysmal subarachnoid hemorrhage; ASA, American Society of Anesthesiologists; MRI, magnetic resonance imaging; ICU, intensive care unit; FiO_2_, fraction of inspired oxygen; COPD, chronic obstructive pulmonary disease; BMI, body mass index.

### Intervention

Blood pressure and vital signs will be monitored with MRI-compatible equipment Philips Expression MR400 (Philips Healthcare, Best, The Netherlands) during scanning and Philips IntelliVue X2 (Philips Healthcare, Best, The Netherlands) in the operating room and ICU. Invasive continuous blood pressure monitoring is achieved via a radial artery catheter with a fluid-filled line and Xtrans® pressure transducer (CODAN TRIPLUS AB, Kungsbacka, Sweden). Electrocardiogram, pulse oximetry, systolic and diastolic pressure, MAP, and end-tidal carbon dioxide (EtCO₂) are continuously recorded using the respective patient monitoring systems, with all data exported to the PDMS. Administered drugs are entered manually into the PDMS. Arterial blood gases will be sampled immediately before and after the intervention and analyzed using ABL90 FLEX PLUS (Radiometer Medical ApS, Brønshøj, Denmark). For MAP-SAH patients, ICP is continuously monitored in the ICU using an intraparenchymal or intraventricular catheter, with values exported to the PDMS.

As a safety measure, blood pressure elevation is carried out prior to transport to the MRI suite in the operating room (MAP-ANE) or ICU (MAP-SAH). During this manipulation, NIRS measurements are obtained with the INVOS™ 5100C (Medtronic, Minneapolis, MN, USA). Baseline MAP is defined by the attending anesthesiologist according to clinical routines, typically 65–70 mmHg. If NE infusion is already required to maintain this level, it is continued at the same dose and documented as the baseline NE dose. For the blood pressure elevation procedure, NE infusion is titrated stepwise every 2 minutes by 0.01–0.04 μg·kg⁻¹·min⁻¹ until a 25% MAP increase or a systolic pressure limit of 160 mmHg in MAP-ANE and 200 mmHg in MAP-SAH is reached. MRI scans will be acquired at both baseline and elevated MAP. NE (Sintetica, Mendrisio, Switzerland) is prepared as a 40 µg/mL solution and administered via a Braun Perfusor Space pump (B. Braun, Melsungen, Germany), with Plasmalyte (Baxter, Deerfield, IL, USA) delivered by Braun Infusomat Space (B. Braun, Melsungen, Germany) as the carrier. The intervention lasts approximately 90 minutes. All participants are monitored by an anesthesiologist, and NE infusion is discontinued at any sign of adverse response.

### Anesthesia management

During MRI acquisition in both MAP-ANE and MAP-SAH, anesthesia is maintained with propofol 20 mg/mL (Baxter, Deerfield, IL, USA) administered as a continuous infusion at 4–8 mg·kg ⁻ ¹·h ⁻ ¹, titrated as needed. An intravenous bolus dose of fentanyl 150–200 μg (B. Braun, Melsungen, Germany) is administered immediately before transfer into the MRI scanner. The depth of anesthesia is assessed continuously by the attending anesthesiologist. Sedation and mechanical ventilation are maintained throughout transport from the operating room (MAP-ANE) or ICU (MAP-SAH) to the MRI suite and during the imaging procedure.

### Outcomes

The primary outcome is the change in total CBF between baseline and elevated MAP, thereby directly testing whether induced hypertension increases CBF. Secondary outcomes include additional perfusion measurement with ASL, characterization of the slope of the MAP–CBF relationship, and analysis of associations between systemic and cerebral hemodynamic parameters, such as cardiac output (CO), systemic vascular resistance (SVR), cerebrovascular resistance (CVR), and arterial compliance. Further, changes in rSO_2_ relative to CBF will be analyzed to evaluate its validity as a surrogate marker. Safety parameters, including arrhythmias, bradycardia, or other adverse responses during NE infusion, are monitored continuously. Events severe enough to require interruption of the procedure and discontinuation of NE infusion are documented in the CRF.

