
### Hemodynamic characteristics

Total CBF is calculated as the sum of blood flow rates (mL/min) in the left and right internal carotid and vertebral arteries. CO is represented by ascending aorta flow rate, stroke volume is derived from CO divided by heart rate. The flows in the external carotid arteries are summed and interpreted as a characterization of peripheral vascular flow. CVR is calculated as (MAP – ICP)/CBF. SVR is calculated as ([MAP – central venous pressure (CVP)]/CO) × 80. CVP is assumed to be 10 mmHg in both groups [27]. ICP is assumed to be 10 mmHg in MAP-ANE [28], whereas in MAP-SAH the recorded mean ICP from the hour preceding the intervention is used. Flow areas are calculated using ROI for all vessels. Arterial compliance will be calculated from PCMRI-derived flow waveforms and simultaneous arterial pressure data as previously described [29]. An overview of measured and derived variables is provided in Table 2.

**Table 2 pone.0338688.t002:** An overview of all measured and derived variables.

Variable	Source/method	Unit

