### Statistical methods

All analyses will be performed using SPSS (IBM Corp., Armonk, NY, USA). Given the relatively small sample size, assumptions of normality cannot be reliably validated; therefore, non-parametric tests will be used. Descriptive statistics will be reported as medians with interquartile range unless otherwise specified. Changes in flow, pressure, resistance, arterial compliance, and vessel area between baseline and elevated MAP will be analyzed using the Wilcoxon signed-rank test. Correlations between systemic and cerebral hemodynamic variables will be explored using Spearman’s rank correlation. A two-sided p-value <0.05 will be considered statistically significant.

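### SVR and CVR are both computed from MAP, so a Spearman test of their association is biased upward: negligibly if MAP is tightly controlled, heavily if both pressure levels are pooled

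*Protocol article*

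**What the plan says.** All references are to the protocol article.

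- **Outcomes** lists, as a secondary outcome, "analysis of associations between systemic and cerebral hemodynamic parameters, such as cardiac output (CO), systemic vascular resistance (SVR), cerebrovascular resistance (CVR") and arterial compliance. The list is illustrative and names no pairs.
- **Statistical methods** gives the test: "Correlations between systemic and cerebral hemodynamic variables will be explored using" Spearman's rank correlation. It then sets one threshold for everything: "A two-sided p-value <0.05 will be considered statistically significant".
- **Hemodynamic characteristics** gives the formulas: "CVR is calculated as (MAP – ICP)/CBF" and "SVR is calculated as ([MAP – central venous pressure (CVP)]/CO) × 80". It also fixes the subtracted pressures: "CVP is assumed to be 10 mmHg in both groups" and "ICP is assumed to be 10 mmHg in MAP-ANE", whereas "in MAP-SAH the recorded mean ICP from the hour preceding the intervention is used".
- **Intervention** puts baseline MAP typically at 65–70 mmHg and titrates to a 25% rise, or to a systolic limit if that is reached first.

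The article does not say whether the correlations use baseline values, elevated values, changes or both levels together. It does not mention that the two resistances share a term.

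**The concern.** When two ratios have the same numerator, they correlate positively even if their denominators are unrelated. Here the shared numerator is also the quantity that the intervention moves on purpose. A Spearman test against zero then no longer answers whether the systemic and cerebral circulations are linked.

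The Introduction states exploring interactions between the two circulations as an objective. A nominally significant SVR–CVR correlation would naturally be read as such an interaction, although the formulas alone could have produced part or all of it. The same mechanism affects MAP against CVR, because MAP sits inside CVR.

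**Working it through.** The plan gives no figure for this association, so there is none to reproduce. The sample size is taken as stated: 18 analyzable per cohort (18/0.90 = 20 enrolled).

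**Step 1: algebra.** In MAP-ANE, CVP = ICP = 10, so SVR/80 = (MAP − 10)/CO and CVR = (MAP − 10)/CBF. The numerators are identical. In MAP-SAH, ICP is one fixed value per patient, so the numerators are MAP − 10 and MAP − ICP and share MAP.

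**Step 2: effect of the intervention.** From a MAP of 67.5 mmHg, a 25% rise gives 67.5 × 1.25 = 84.4. MAP − 10 goes from 57.5 to 74.4, a rise of 29%. (From 65 mmHg the rise is 29.5%; from 70 mmHg, 29.2%.) If neither flow changes, SVR and CVR both rise by 29%.

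**Step 3: approximate induced correlation at one level.** r ≈ CVx²/(CVx² + CVy²), where CVx is the coefficient of variation of MAP − 10 and CVy that of CO and of CBF. The documents give neither; CVy is assumed to be 15–25%.

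- MAP SD 1.5 mmHg: CVx = 1.5/57.5 = 2.6%, r ≈ 0.01–0.03.
- MAP SD 5 mmHg: CVx = 8.7%, r ≈ 0.11–0.25.
- MAP SD 10 mmHg: CVx ≈ 17%, r ≈ 0.32–0.56.

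**Step 4: simulation.** n = 18, CO and CBF independent, MAP-ANE numerators, Spearman at two-sided 0.05, 3,000 runs per setting. Assumed: flow CV 15–25%, within-patient noise 10%, and the spreads shown.

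| SVR–CVR data used | Assumed spread | Mean rho | p<0.05 |
|---|---|---|---|
| One level | MAP SD 1.5 mmHg | 0.00–0.06 | 4–6% |
| One level | MAP SD 5 mmHg | 0.10–0.23 | 7–15% |
| One level | MAP SD 10 mmHg | 0.29–0.54 | 24–69% |
| Change | rise SD 2 points | 0.02–0.03 | 5–6% |
| Change | rise SD 5 points | 0.12–0.19 | 8–13% |
| Change | rise SD 10 points | 0.38–0.42 | 37–44% |
| Both levels pooled | all of the above | 0.23–0.64 | 30–99% |

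CO against CBF directly gave rho about 0 and 4–6% throughout. Halving the within-patient noise to 5% (flow CV 20%, MAP SD 5 mmHg, rise SD 5 points) raised the change-score rate to 27–44%, so the result is sensitive to that assumption.

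**Step 5: mid-range assumptions.** With CO CV 20%, CBF CV 18% and within-patient change SD about 9%, tightly held baseline values gave rho 0.01–0.02 and about 5%. Change scores gave 5% at a rise SD of 2 points and 33–34% at 8 points. Pooled levels gave 51–85%.

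**Step 6: how much of the pooled figure is the formula.** Pooled CO against CBF, which share no term, was already significant in 14–16% of runs, because two readings per patient were treated as independent. The excess over that comes from the shared term. It appears even with tight pressure control: at MAP SD 1.5 mmHg, rise SD 2 points and flow CV 20%, pooling gave rho about 0.30 and 46%.

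**Step 7: related cases.** With an assumed MAP-SAH ICP of 12 mmHg (SD 4) and flow CV 20%, baseline rho was 0.14 at MAP SD 5 mmHg and 0.39 at SD 10 mmHg, almost as in MAP-ANE. For MAP against CVR, with MAP SD 1.5–8 mmHg, false positives were 7–81% at baseline and 95–100% pooled.

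**The case against.** The strongest reply is that the article never commits to this test. Its parameter list is illustrative, its correlations are exploratory, and pairs and units of analysis are usually settled in an analysis plan. That limits the point but does not remove it. CVR is the only specifically cerebral quantity named in the list, SVR is its systemic counterpart, and the formulas, test and threshold are all stated.

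A reader might go further and infer that a spurious association will appear. The documents do not support this. With MAP within the typical baseline range, or a uniform rise, the error rate is close to nominal. Equally, no passage plans to pool the two levels. The design is described as paired, and changes are tested with a paired method. The pooled figures show what happens if pooling is done, and part of them is pseudo-replication.

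A third reply is that if MAP truly rises while flows stay constant, both resistances have truly risen, so their joint movement is no mere artefact. This stands as a description of the pressure intervention. It does not make the correlation separate evidence that the two circulations are linked.

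Finally, CVR against CBF is also coupled, but both are cerebral quantities and fall outside the stated outcome.

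**Conclusion.** The point holds in conditional form. The shared MAP term is certain from the stated formulas, and for unrelated flows the bias is upward. Its size is not fixed by the documents. It is negligible under tight pressure control at one level or with a near-uniform rise. It is moderate, about 10–34% false positives, at an assumed MAP SD of 5–8 mmHg or rise SD of 5–8 points; the systolic limits could produce uneven rises. It is large, about 50–85%, if both levels are pooled, against about 15% from repeated readings alone. These rates rest on the assumed flow variability and within-patient noise given above, and wider assumptions widen them.

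The affected outcome is secondary and exploratory. The primary outcome and the sample size do not depend on it.

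**What to change.** Specify the following before analysis:

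1. Test the systemic–cerebral association on the independently measured flows: log change in CO against log change in total CBF, one value per participant, within each cohort.
2. Report SVR–CVR and MAP–CVR descriptively, without p-values. Alternatively, test them against a permutation null that shuffles the flows between participants while keeping each patient's MAP, and recomputes the resistances each time.
3. Do not pool baseline and elevated readings as if they were independent.

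Phase-contrast MRI already supplies both flows, so this changes wording only and needs no new data. The cost is fewer nominally significant exploratory correlations.

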## Discussion

This study protocol addresses the uncertainty surrounding the relationship between MAP and CBF during anesthesia and critical illness, with a focus on NE-induced blood pressure elevation. By applying standardized methodology across two distinct but related patient populations, elective anesthesia patients and sedated aSAH patients, we will be able to compare MAP–CBF relationships under different physiological conditions. The use of PCMRI and ASL allows direct and quantitative assessment of global cerebral blood flow, which overcomes the limitations of surrogate methods such as NIRS.

A major strength of the study is its design, combining invasive hemodynamic monitoring with advanced MRI-based flow measurements. This multimodal approach enables us to test the hypothesis that blood pressure augmentation with NE does not increase CBF, and to assess whether NIRS can serve as a valid bedside proxy for CBF changes. The parallel investigation of two study populations enhances generalizability, as one group represents controlled perioperative conditions while the other reflects neurocritical care after aSAH.

Several challenges and limitations must be acknowledged. MRI measurements are not feasible at the bedside, which may limit clinical applicability. However, the purpose of this study is not to provide a bedside monitoring tool, but to investigate fundamental pathophysiological mechanisms linking MAP and CBF under anesthesia and in critical illness. By establishing such principles with quantitative MRI, subsequent research can evaluate whether surrogate measures such as NIRS may reliably capture comparable information in the clinical setting.

Transport of sedated and ventilated ICU patients carries inherent risks, although these will be mitigated through rigorous safety procedures and continuous supervision by an anesthesiologist. Sample size is relatively modest, which restricts subgroup analyses and may limit statistical power for secondary outcomes. Finally, while inclusion of both study populations enhances the clinical relevance of the results, generalization beyond these groups should be made cautiously.

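### The safety recording rule depends on norepinephrine running and being stopped, so an adverse event during MAP-SAH transport, a risk the protocol itself names, may not qualify for recording

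*Protocol article*

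**What the plan says.** The Outcomes section makes two statements about safety. The first sets the scope: "Safety parameters, including arrhythmias, bradycardia, or other adverse responses during NE infusion, are monitored continuously". The second sets what is written down: "Events severe enough to require interruption of the procedure and discontinuation of NE infusion are documented in the CRF".

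The Discussion names a risk of the study procedure: "Transport of sedated and ventilated ICU patients carries inherent risks". It says this risk will be "mitigated through rigorous safety procedures and continuous supervision by an anesthesiologist". No outcome or record is attached to it.

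The MAP-SAH flow (legend to Fig 4) places the first pressure elevation in the ICU as a tolerance check, then transport to MRI (step C), scanning at both pressure levels (step D), transport back (step E) and finally "Continued neurointensive care and monitoring" (step F). The Intervention section says that NE already needed to hold baseline pressure is continued at its existing dose. It also says that vital signs are recorded continuously and exported to the patient data management system (PDMS).

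**The concern.** The safety scope is defined by the drug, whereas the risk named in the Discussion arises from moving the patient. The CRF rule narrows the scope further, because it requires that an infusion be stopped. Where no infusion runs in transit, a transport event is out of scope on the first statement and unrecordable on the second.

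At stake is how the safety record will read. A statement that no events were documented would naturally be taken to cover the whole study procedure, including the two transports made for research. Under the stated rule it would cover only events while NE was running, and of those only the ones that ended the procedure and the infusion.

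**Working it through.** The plan gives no safety figure to reproduce, so the check sets the passages side by side.

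**Inputs**
- Scope: adverse responses while NE is infused (Outcomes).
- CRF threshold: procedure interrupted and NE discontinued (Outcomes).
- Transports: two per MAP-SAH patient, steps C and E (Fig 4 legend).
- NE outside the elevation steps: continued only where already needed at baseline (Intervention).
- Enrolment: 20 per cohort (Sample size). This follows from the 18 analyzable pairs and 10% attrition: 18 / 0.9 = 20.

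**Step 1: a patient without baseline NE.** The ICU elevation is a check made before transport, and the article does not say that the infusion runs on to the scanner or back. If it does not run, an event in transit fails the scope statement. It also fails the CRF rule, since that rule joins two conditions and the second cannot occur. This holds even for an event serious enough to abandon the scan. Such a patient might appear only as one of the 20 − 18 = 2 lost pairs that the attrition allowance covers.

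**Step 2: a patient on baseline NE.** The infusion may continue in transit, so the event is within the scope statement. It reaches the CRF only if it also meets the threshold.

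**Step 3: how many transports.** With k of the 20 MAP-SAH patients on baseline NE, the transports outside the scope number up to 2 × (20 − k). The documents do not give k, so the range is:

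| k (assumed) | Transports outside scope, at most |
|---|---|
| 0 | 40 |
| 10 | 20 |
| 20 | 0 |

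**Step 4: what a zero count would mean.** If no event were recorded in 20 patients, the exact one-sided 95% upper bound on the event rate would be 1 − 0.05^(1/20) = 13.9% (two-sided: 1 − 0.025^(1/20) = 16.8%). That bound applies only to events the rule can capture. For transport events without NE running, a recorded zero carries no information and supports no bound.

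**Step 5: does the PDMS close the gap?** The Intervention section names monitors for scanning, the operating room and the ICU, and describes intracranial pressure monitoring in the ICU. It names none for transit. Even where vital signs are exported, the Outcomes section does not make them part of the safety record.

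**The case against.** The strongest reply is that this is a condensed article. Adverse event definitions and reporting windows are commonly left to the full protocol, and the schedule figures are not shown. These are small physiological studies in which no safety conclusion is planned. Transport is supervised, tolerance is checked beforehand, and vital signs go to the PDMS. On that view the issue is classification only.

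Much of this stands, and it keeps the point small. It does not remove it, because the Outcomes section does not leave the matter open: it states a scope and a recording rule, and both bypass a risk that the same article names. Supervision lowers the risk but does not record it.

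Three stronger readings are tempting, and the documents do not support them.
- *Late MAP-SAH patients have no follow-up.* The Study design section says "MAP-SAH is planned to continue until October 2030, with follow-up concluding at the same time". That is a shared end month. It gives no last enrolment date and no follow-up length per patient, and recruitment may stop earlier.
- *Delayed cerebral ischemia is a named post-procedure harm that goes uncounted.* The Introduction says "patients remain at risk of delayed cerebral ischemia (DCI) and associated neurological deficits during the early phase", but as part of the disease course after aneurysm treatment. Its remark on induced hypertension, "its effects on CBF remain uncertain, and the therapy carries risk", is general and names no event or time window.
- *Late patients could not confirm consent.* Confirmation is sought if capacity returns, and nothing ties it to the follow-up period.

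**Conclusion.** The point holds in a narrow form and is minor. The safety scope and CRF rule in the Outcomes section do not cover the transport risk stated in the Discussion. In MAP-SAH patients without baseline NE, an adverse event on either transport cannot meet the rule as written.

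This rests on two assumptions: that NE is not running in transit in those patients, which the article neither requires nor excludes, and that the full protocol has no wider rule. If it has one, the article's wording should be brought into line with it.

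The size is at most 40 transports in MAP-SAH, and fewer for each patient already on NE. No count of missed events can be given without a transport event rate, which the documents do not supply. The primary CBF analysis is unaffected.

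**What to change.** Reconcile the Outcomes section with the Discussion:
- Define the safety recording window, for both cohorts, as running from the start of the first NE elevation, through both transports where they occur, to handover in the ICU (MAP-SAH) or recovery (MAP-ANE).
- Document adverse events in that window whether or not NE was running and whether or not it was stopped, using PDMS vital signs and the clinical record.
- Report which events occurred in transport and whether NE was running at the time.

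Recruitment is under way in both cohorts, so the same abstraction should be made retrospectively for patients already studied.

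The cost is a few lines of text and a short record abstraction for 20 patients per cohort. The event count may look less favourable. The change concerns recording only and alters no dose, pressure target or stopping rule.
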